#### Recruitment

All the GPs will receive an e-mail presenting the study as a work on the topic of ‘sexual dysfunction’. Volunteer GPs will be recruited. We asked the GPs from both groups at the beginning of the study whether they had ever benefited from specific training in communication skills before this study. This specific question will allow us to evaluate whether GP group differences result from the training versus no training conditions. The cluster will be identified before the randomisation. All the participants will receive a certificate at the end of the ‘usual care’ and ‘intervention’ sessions. The training sessions and workshop will take place within a suitable schedule for the GPs involved, in a pleasant and constructive atmosphere. One phone call per month, and two e-mails per month will be made to remind the GP participants to include patients. The slides presented in both the CG and the IG will be at the GPs’ disposal after the sessions. In each communication, the research team will insist on knowing the possible issues encountered by the GPs throughout the entire process. The enrolment period will extend over 12 months.

### Assignment of interventions (for controlled trials)

#### Allocation

The randomisation is stratified by region, and by physician’s gender, using a random block randomisation sequence generated in Stata software (version 13, StataCorp, College Station, TX, USA). The GP’s surgery is the unit of randomisation. A GP investigator and their patients will be assigned to the same group. The patients will not know to which group their GP has been randomised. Investigators from the same GP’s surgery are randomised within the same group in order to avoid contamination bias.

The participating GPs will be randomised using Stata version 13 (StataCorp, College Station, TX, USA) which is an online, central randomisation service. Allocation concealment will be ensured as the service will not release the randomisation code until the GP has been recruited into the trial in each region.

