### Sample size estimation

As this study had been designed as a cluster randomised trial, a sample size estimation was proposed which would highlight a significant difference between the two randomised groups in terms of the incidence of new cases of patients bringing up the topic of PE with their GP. It takes into account an intra-cluster correlation coefficient (ICC) varying between 0.05 and 0.20 and includes a recruitment of around 15 patients per GP [29]. In order to take into account between- and within-GP variability, expressed by intra-class correlation coefficient (ICC), this sample size must be increased by an inflation factor: 1 + (*m* − 1). ICC, with *m* the (mean) number of patients included by each GP. According to the literature [29, 30], it is not so easy to determine the appropriate value of ICC. It depends of many factors. We have chosen to fix ICC between 0.05 and 0.20, according to previous references. With 15 patients included by each GP, sample size estimation was 360 for ICC equals 0.05 and 800 for ICC at 0.20, and around 960 for ICC at 0.25. Furthermore, it is usual to observe a Hawthorne effect in this type of study. In our feasibility study, the incidence of patients who brought up PE with their GP in the CG was 6.6%. Following the guideline of PE updated by the ISSM, ‘5% of the population have an ejaculation latency of less than 2 minutes’ [8]. We estimated the incidence in the CG at around 5%. Usually in individual randomisation, *n* = 101 patients in total is necessary to highlight an absolute difference between 5 and 20%. For a two-sided type I error, *α* equals 0.05 and has a statistical power of 90%. Also, taking these aspects into account 600 patients, recruited by 40 GPs, must be included and then divided into 300 patients in each arm.

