#### Statistical methods

Analyses will be performed using Stata software, version 13 (StataCorp, College Station, TX, USA). All data will be analysed on intention to treat. The tests will be two-sided, with a type I error set at *α* = 0.05. Baseline characteristics (GPs and their patients) will be presented for each randomisation group as the mean ± standard deviation (SD) or the median (interquartile range) according to statistical distribution for continuous data and according to the number of patients and associated percentages for categorical parameters.

The comparisons between the randomised groups will be carried out using the Student *t* test or the Mann-Whitney test where appropriate, (1) normality verified by the Shapiro-Wilk test and (2) homoscedasticity by the Fisher-Snedecor test for quantitative parameters and using chi-squared or Fisher’s exact tests for categorical variables.

Outcomes will pertain to the cluster level using usual statistical tests and with more specific approaches at the individual level. Hierarchical regression models (generalised linear mixed model due to binary endpoint) will be performed as primary analysis: (1) to estimate the effect of intervention on the incidence of new cases of patients suffering from acquired and lifelong PE, natural variable PE and premature-like ejaculatory dysfunction and (2) to take into account the variability between and within, the GP cluster groups. Intra-class correlation coefficients will be presented by arm with a 95% CI. Then, GP characteristics (gender, age, geographical area) or patient characteristics (age, socioeconomic status) should be considered as covariate (fixed effects in mixed models) in adjusted multivariable analyses. The adjusted and unadjusted results will be presented: absolute numbers of patients who have raised the topic of PE with their related GP, relative risks and 95% CIs.

For secondary endpoints, comparisons at the individual level between randomised groups will be performed using an analysis of covariance for correlated data with the baseline score as a covariate, as suggested by Klar and Darlington [31] for the SF-12 quality of life scores. Results will be expressed as effect-sizes and 95% CIs. The PEDT will be analysed as a quantitative score using statistical methods described for the SF-12 quality of life and as a binary outcome (< ≥ 11) with the use of a generalised linear mixed model.

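### Surgeries are named as the unit of randomisation, but the sample size, and on its natural reading the primary model, take the GP as the cluster; if GPs of one surgery are correlated, standard errors are too small

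*Protocol article*

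**What the plan says.** The Allocation section names the randomised unit: "The GP’s surgery is the unit of randomisation". It foresees surgeries with several participating GPs: "Investigators from the same GP’s surgery are randomised within the same group in order to avoid contamination bias". The same section also says "The participating GPs will be randomised using Stata version 13", and sets the strata thus: "The randomisation is stratified by region, and by physician’s gender". Gender belongs to a GP, not to a surgery.

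The Sample size estimation section ties the ICC to variability between and within GPs. It defines the cluster size m in the design effect as "the (mean) number of patients included by each GP", about 15, and arrives at 600 patients from 40 GPs. The ICC range is 0.05 to 0.20.

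The Statistical methods section makes a generalised linear mixed model the primary analysis, intended among other things "to take into account the variability between and within, the GP cluster groups".

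The article gives no number of surgeries, no number of patients per surgery, no surgery-level ICC and no surgery term in the model.

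**The concern.** A valid comparison has to allow for correlation at the level at which allocation was made. GPs of one surgery always land in the same arm, so any correlation between them adds to the variance of the treatment contrast. A random intercept for GP alone does not pick this up.

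The protocol's own reason for keeping colleagues together is that they may influence one another. Under Intervention, the workshop may also be held at the GP's surgery, so colleagues in that arm may be trained together.

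Three things are at stake:
- the type I error and interval width of the primary result;
- the number of independent units behind the stated power;
- whether the stratified allocation can be carried out for a surgery whose participating GPs are of both sexes.

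**Working it through.** **Inputs from the article.** Rates 5% and 20%, two-sided α 0.05, power 90%, m = 15 patients per GP, ICC 0.05 to 0.20, 40 GPs, 300 patients per arm.

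**Inputs that are assumed, because the article gives none.** The fraction p of GPs who take part in pairs from one surgery: 0.2, 0.5 or 1. The share f of the between-GP variance that belongs to the surgery: 25% to 100%. The correlation between patients of different GPs in one surgery is then f × ICC.

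**Step 1: the plan's own figures.** The usual formula for two proportions gives 101 per arm. With design effect 1 + 14 × ICC:
- ICC 0.05: 2 × 101 × 1.7 = 343 (stated 360)
- ICC 0.20: 2 × 101 × 3.8 = 768 (stated 800)
- ICC 0.25: 2 × 101 × 4.5 = 909 (stated about 960)

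The stated totals are not reproduced exactly; these results are about 4–5% lower. They are close enough to confirm that the GP is the cluster in the planning. (That 101 comes out per arm while the article calls it a total, and that 600 is below 800, are separate matters.)

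**Step 2: variance when the surgery is the randomised unit.**

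Design effect = 1 + 14 × ICC + 15 × p × f × ICC

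True SE ÷ SE from a GP-level analysis = √[(1 + 14 × ICC + 15 × p × f × ICC) ÷ (1 + 14 × ICC)]

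Real two-sided α ≈ 2 × [1 − Φ(1.96 ÷ ratio)]

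Example, all paired, ICC 0.20, f = 50%: 3.8 + 15 × 0.10 = 5.3; ratio √(5.3 ÷ 3.8) = 1.18; α ≈ 9.7%.

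| GPs paired | ICC | Design effect, f = 25% to 100% | SE ratio | α by formula | α by simulation |
|---|---|---|---|---|---|
| all | 0.20 | 4.55 to 6.80 | 1.09 to 1.34 | 7.3 to 14.3% | about 7.5 to 15% |
| all | 0.05 | 1.89 to 2.45 | 1.05 to 1.20 | 6.3 to 10.3% | about 6 to 10.7% |
| half | 0.20 | 4.18 to 5.30 | 1.05 to 1.18 | 6.2 to 9.7% | about 6 to 10% |
| a fifth | 0.20 | 3.95 to 4.40 | 1.02 to 1.08 | 5.5 to 6.9% | about 5.5 to 7% |
| a fifth | 0.05 | 1.74 to 1.85 | 1.01 to 1.04 | 5.2 to 6.0% | about 5 to 6% |

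The simulation draws GP means with no treatment effect, 20 GPs per arm and 15 patients each, and applies a t-test to the GP means. The same test on surgery means rejects at about 5% in every setting.

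**Step 3: power of 600 patients before attrition,** with effective n per arm = 300 ÷ design effect:
- ICC 0.20: 300 ÷ 3.8 = 78.9, power 82% on the plan's own cluster. With all GPs paired and f = 25 / 50 / 100%, power is 75 / 68 / 57%.
- ICC 0.05: power is 99% on the plan's own cluster and stays at about 95% or more with all GPs paired.

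**Step 4: no effect.** With p = 0 or f = 0 the added term is zero and the ratio is 1.

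**The case against.** The strongest reply concerns the model. The phrase about GP cluster groups is loose. The Recruitment section says that the cluster is identified before randomisation, and Allocation says that the surgery is randomised, so the phrase could mean surgeries. An article also commonly leaves the exact random-effects structure to the full protocol or SAP. This stands in part. The GP is the more natural reading, since the sample size section defines clustering by GP, but it remains an inference. The type I error figures depend on it, because the sample size mismatch affects only power.

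The second reply is that multi-GP surgeries may be few. The GPs are individual volunteer trainers, contacted by e-mail across four regions, and the article does not say how many share a surgery. This stands, and is why the range includes a fifth paired and ICC 0.05.

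A reader might go further and infer that standard errors are too small at every surgery with more than one GP, that the true type I error is about 15%, or that colleagues share patients. The documents support none of these. The first also needs a positive within-surgery correlation, which the contamination argument makes plausible but does not quantify. The second needs every GP paired, the top ICC, and no difference between colleagues beyond sampling error. The third is stated nowhere.

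Finally, the simulated test is a t-test on GP means, not the planned mixed model, so the percentages are indicative.

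**Conclusion.** The concern holds in conditional form. Allocation contradicts itself on the randomised unit, the gender stratum is undefined for surgeries with participating GPs of both sexes, and the sample size is built on a different unit from the one named as randomised. Confidence in these points is high. That the primary model omits the surgery is the natural reading, held with moderate confidence.

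The consequence depends on two quantities that the article does not give. It ranges from nil, through about 5–7% type I error if a fifth of GPs are paired, to about 7.5–15% if all are paired at ICC 0.20. The gender point is separate and does not bear on the standard errors. The plan should be changed because the correction is cheap and is right whatever these quantities turn out to be.

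**What to change.** - **Statistical methods:** state that the primary mixed model has a random intercept for surgery, with GP nested in surgery where a surgery has more than one participating GP. Report the surgery-level ICC.
- **Sample size estimation:** give the number of surgeries and of patients per surgery, and restate the design effect and the resulting power on that basis, without enrolling more.
- **Allocation:** name one unit of randomisation. Either define the gender stratum for a surgery, or stratify surgeries by region only and keep GP gender as a covariate. If allocation has already been carried out, report the rule that was used for surgeries with GPs of both sexes.

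The cost is wording plus a surgery identifier, which allocation by surgery already requires. Trial status says that recruitment was incomplete at submission. If surgeries supply several GPs, intervals will be somewhat wider and the stated power less favourable. If each supplies one, the results do not change.

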#### Blinding

Due to the nature of the intervention, neither the GPs from the intervention team nor the researchers recruiting the GPs can be blinded to allocation, but it will be strongly impressed upon them that they must not disclose the allocation status of the participants at the follow-up assessments. The objective of this measure is that a GP from the CG should not know that they are in a CG. An employee outside the research team will collect the questionnaires (SF-12 and PEDT) and feed data into the computer on separate datasheets so that the researchers can analyse data without having access to information about the allocation. The patients will be blinded to the allocation of their GP and the trial aim.

### Data collection, management, and analysis

#### Data collection methods

The questionnaires filled in by the GPs and the patients will be mailed to the main centre in Brest. The data from these questionnaires will be implemented in an Excel® table. The data collection will be stored at the Brest centre.

A letter will be sent to the patients to remind them to mail the second SF-12 questionnaire and the PEDT questionnaire if they have not returned them 5 weeks after the consultation.

#### Data management

Original study forms will be entered and kept on file at the participating site. A subset will be requested later for quality control; when a form is selected, the participating site staff will access that form, copy it, and send the copy to the Data Coordinating Centre.

Participant files are to be stored in numerical order and stored in a secure and accessible place and manner. Participant files will be maintained in storage for a period of 15 years after completion of the study.

#### Statistical methods

Analyses will be performed using Stata software, version 13 (StataCorp, College Station, TX, USA). All data will be analysed on intention to treat. The tests will be two-sided, with a type I error set at *α* = 0.05. Baseline characteristics (GPs and their patients) will be presented for each randomisation group as the mean ± standard deviation (SD) or the median (interquartile range) according to statistical distribution for continuous data and according to the number of patients and associated percentages for categorical parameters.

The comparisons between the randomised groups will be carried out using the Student *t* test or the Mann-Whitney test where appropriate, (1) normality verified by the Shapiro-Wilk test and (2) homoscedasticity by the Fisher-Snedecor test for quantitative parameters and using chi-squared or Fisher’s exact tests for categorical variables.

Outcomes will pertain to the cluster level using usual statistical tests and with more specific approaches at the individual level. Hierarchical regression models (generalised linear mixed model due to binary endpoint) will be performed as primary analysis: (1) to estimate the effect of intervention on the incidence of new cases of patients suffering from acquired and lifelong PE, natural variable PE and premature-like ejaculatory dysfunction and (2) to take into account the variability between and within, the GP cluster groups. Intra-class correlation coefficients will be presented by arm with a 95% CI. Then, GP characteristics (gender, age, geographical area) or patient characteristics (age, socioeconomic status) should be considered as covariate (fixed effects in mixed models) in adjusted multivariable analyses. The adjusted and unadjusted results will be presented: absolute numbers of patients who have raised the topic of PE with their related GP, relative risks and 95% CIs.

For secondary endpoints, comparisons at the individual level between randomised groups will be performed using an analysis of covariance for correlated data with the baseline score as a covariate, as suggested by Klar and Darlington [31] for the SF-12 quality of life scores. Results will be expressed as effect-sizes and 95% CIs. The PEDT will be analysed as a quantitative score using statistical methods described for the SF-12 quality of life and as a binary outcome (< ≥ 11) with the use of a generalised linear mixed model.

A sensitivity analysis will be carried out to study the attrition bias and to characterise the statistical nature of missing data in order to propose the most appropriate missing data imputation method. More precisely, a maximum bias approach will be performed for the primary outcome and a multiple imputation method for secondary outcomes.

The analysis of the type of strategies used by the GPs in the IG will be descriptive and exploratory.

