The first study on this topic occurred in 2009 with a qualitative study to bring to the fore the strategies used by GPs to initiate the discussion on PE. Eleven GPs participated in semi-structured interviews composed of open-ended questions for exploration and closed questions to refine the participants’ answers [22]. According to the content analysis of the interviews transcribed verbatim, six different strategies used by the GPs to tackle the subject were identified (described in the ‘Methods’ section).

The main aim of this study is to investigate whether training in communication skills with these six strategies is more effective than usual care on the incidence of patients bringing up the topic of PE with their GP.

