## Methods

### Outcome

The primary outcome is the incidence of patients bringing up the topic of PE with their GP.. This was undertaken in the group where the GPs received training in communication skills directed towards this pathology, compared with the patients who received the usual care procedures.

The secondary outcome relates to the variation in the quality of life of patients after they have addressed the topic of PE as measured by the SF-12 questionnaire.

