#### Data collection

##### Outcomes and measurements

To measure the incidence of patients suffering from acquired and lifelong PE, natural variable PE and premature-like ejaculatory dysfunction, the final diagnosis of PE will be made by referring to the answers given to the Premature Ejaculation Diagnostic Tool (PEDT) sent back by the patient 4 weeks after the consultation (please refer to the ‘Measurements’ section). The patients suffering from PE will be identified if their score is higher than 9 on the PEDT. The PEDT questionnaire is an extensively validated, self-report measure that can systematically assess DSM-IV-TR criteria to provide accurate diagnoses of PE/no-PE [26]. It is a screening tool with cut-off scores, brief and easy to administer, and recommended by the International Society of Sexual Medicine [8, 26, 27]. The self-report questionnaire, in our opinion, seems to handle delicate, intimate questions with appropriate sensitivity. We followed a linguistic and cultural validation procedure to obtain a French version of the questionnaire. Additional file 4 is an abstract describing the procedure we followed.

Patients in the two groups will have to complete a self-report questionnaire on quality of life, the SF-12 questionnaire, in a French-validated version right after the consultation, and again, 4 weeks after the consultation [28]. The SF-12 questionnaire right after the consultation will be available in the waiting room. The SF-12 questionnaire, 4 weeks after the consultation, will be posted or e-mailed to the patient. The SF-12 is a self-report questionnaire exploring quality of life [28]. The original questionnaire contained 36 items divided into eight scales, the SF-36 [28]. The SF-12 was created to shorten the responses and included one or two items from each of the eight SF-36 scales. The French version of the SF-12 is correlated to the SF-36 [28]. We chose a general quality of life self-report questionnaire for several reasons. A generic scale was useful to avoid influencing patients in the CG. The availability of a validated French version was another argument supporting the choice of this scale [28].

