### Feasibility

As far as we are aware, this interventional multicentre study will be the first one concerned with PE in the area of primary health care. We created a pilot intervention study in primary care in order to estimate the feasibility of such a study design, as well as the incidence of diagnosed PE with, and without, the use of strategies. Thirteen GPs agreed to participate in the IG, six of whom included their patients in the study. Twenty-four GPs participated in the CG, 13 of whom included their patients in the study. The GPs in the IG included 26 of their patients in the study. They identified eight patients suffering from PE: 30.8%. The GPs in the CG included 61 of their patients. Among them, four were suffering from PE: 6.6% (*p* value = 0.004, OR = 6.6768, 95% confidence interval (CI) (1.55; 34.40)).

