## Discussion

This intervention study will be the first concerned with PE in the area of primary health care. Six different strategies for tackling the subject were brought to light after a qualitative phase with GPs was compared with usual care procedures in primary health care. A French version of the Premature Ejaculation Diagnostic Tool will be used to detect patients from the IG and the CG who suffer from PE.

One major limitation is the unblinded GPs in the IG. As the intervention is based on training in strategies to tackle PE, it was impossible to leave them blind to the main aim of the study. The evaluation of the diagnosis of PE will be made by the GP. This limitation is counterbalanced by the fact that the PEDT sent after 1 month will also contribute to making the positive or negative diagnosis of PE.

We selected our participants via an e-mail, mentioning a study on ‘sexual dysfunction’ at the first step of the study. We wanted to inform them about the topic raised during the intervention. The GPs in the CG knew that the study was investigating sexual dysfunction: this could lead to increased awareness of sexual dysfunction, including PE, and thereby lead to an increase in the rate of consultations where PE was raised. We did not mention ‘sexual dysfunction’ on any other occasion to the CG.

The definition of PE references a pathology concerned with ‘vaginal penetration’. However, we want to enlarge the study to include men with a different sexual orientation. We did not include any questions about heterosexual or homosexual orientation in our questionnaires.

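### The primary mixed model is written for new cases of men suffering from PE, but the aim, primary outcome and sample size concern the topic of PE being raised with the GP

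*Protocol article*

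**What the plan says.** Four places define the trial's question as an event in the consultation:

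- Outcome section: "The primary outcome is the incidence of patients bringing up the topic of PE with their GP". The Abstract (Methods) agrees.
- End of the Background: whether training "is more effective than usual care on the incidence of patients bringing up the topic of PE with their GP".
- Sample size estimation: 5% v 20% is stated for patients bringing up the topic.

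Statistical methods describes the main analysis differently. "Hierarchical regression models (generalised linear mixed model due to binary endpoint) will be performed as primary analysis", and the first stated purpose is "to estimate the effect of intervention on the incidence of new cases of patients suffering from acquired and lifelong PE, natural variable PE". The sentence then names a fourth category, the premature-like type.

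Other sections bear on how such a case would be identified:

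- Outcomes and measurements uses the same four PE categories and says that "the final diagnosis of PE will be made by referring to the answers given to the Premature Ejaculation Diagnostic Tool (PEDT") returned 4 weeks after the consultation. It adds: "The patients suffering from PE will be identified if their score is higher than 9 on the PEDT".
- Discussion: "The evaluation of the diagnosis of PE will be made by the GP", with the PEDT at one month contributing.
- Statistical methods, same paragraph as the primary model: the results to be presented are the numbers of patients who raised the topic, with relative risks. The next paragraph puts the PEDT under secondary endpoints, dichotomised at 11.
- Monitoring: the interim analysis of the primary endpoint waits until half of the patients have completed the SF-12 and the PEDT.

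**The concern.** Raising PE in a consultation, having PE on a questionnaire four weeks later, and being diagnosed with PE by the GP are three different binary variables. A communication workshop can directly change the first. It has no evident way to make more men have PE. Treatment started at the visit, which the workshop also covers, could only lower PEDT scores in the intervention arm.

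A statistician who follows the primary-model sentence, and looks up the case definition where the same categories appear, would model PEDT-defined PE. That endpoint has no planned effect size and depends on a questionnaire that patients must send back. With two candidate endpoints for the primary analysis, the choice could also be made after the results are seen.

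**Working it through.** The contradiction is textual and needs no calculation. The arithmetic only shows what depends on it.

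**Side by side**

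| Place in the article | Endpoint |
|---|---|
| Abstract, Background, Outcome, Sample size estimation | topic of PE raised with the GP |
| Statistical methods, primary model | new cases of patients suffering from PE |
| Statistical methods, results to be presented | topic raised |
| Outcomes and measurements | PE by 4-week PEDT, above 9 |
| Statistical methods, secondary endpoints | PEDT, cut-off 11 |
| Discussion | PE diagnosed by the GP, PEDT contributing |
| Monitoring | interim on the primary endpoint, after PEDT completion |

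**Pilot.** Feasibility says of the intervention GPs "They identified eight patients suffering from PE: 30.8" per cent (8/26 = 30.8%; control 4/61 = 6.6%). The Abstract and Sample size estimation describe the same 6.6% as the topic being raised.

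**The plan's own figure.** Inputs from Sample size estimation: p1 = 0.05, p2 = 0.20, two-sided α = 0.05, power 90%.

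n per arm = [1.960·√(2·p̄·(1−p̄)) + 1.282·√(p1(1−p1) + p2(1−p2))]² / (p2−p1)², with p̄ = 0.125

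= [1.960·√0.21875 + 1.282·√0.2075]² / 0.15² ≈ 100.1, rounded up to 101.

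The 101 is therefore reproduced per arm (202 in total), although the article calls it a total. That is a separate matter and does not affect this point.

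**Power for topic raised, 5% v 20%.** Design effect = 1 + (m−1)·ICC. Effective n per arm = (patients per arm) / (design effect). Power = Φ{[0.15·√n − 1.960·√0.21875] / √0.2075}. Loss rates are from the Abstract (GPs 10%, patients 20%); the ICC range is from Sample size estimation.

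| Evaluable patients | ICC 0.05 | ICC 0.20 |
|---|---|---|
| 40 × 15 = 600 | 300/1.70 = 176.5 → 99.1% | 300/3.80 = 78.9 → 81.9% |
| 36 × 15 = 540 (GP loss) | 270/1.70 = 158.8 → 98.4% | 270/3.80 = 71.1 → 77.7% |
| 36 × 12 = 432 (GP and patient loss) | 216/1.55 = 139.4 → 97.0% | 216/3.20 = 67.5 → 75.6% |

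The last row is the case of an endpoint that needs the returned PEDT while 5% v 20% still holds.

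**Power if the endpoint is PEDT-defined PE alone.** The article gives no effect size for it. Assume that training changes disclosure and not the number of enrolled men with PE. Then p1 = p2 whatever the common rate, the expected difference is 0, and the rejection probability is α = 5%.

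Relaxing this, with assumed differences of 3 to 5 points from an assumed base of 5% to 30% and 432 evaluable patients, power runs from about 6% (base 30%, 3 points, ICC 0.20) to about 35% (base 5%, 5 points, ICC 0.05).

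**The case against.** The strongest defence is that this is loose wording, not a switch of endpoint. The primary-model sentence does not mention the PEDT. The same paragraph promises results as numbers of patients who raised the topic. The PEDT has its own mixed model under secondary endpoints, which would largely duplicate the primary model if that already used PEDT status. The authors also use case and topic raised interchangeably: the pilot control rate carries both labels, and Sample size estimation speaks of new cases of patients bringing up the topic.

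Most of this stands as evidence of intention, and topic raised may well be what was meant. It also rules out two stronger readings. A reader might infer that the main analysis definitely tests PEDT status; the documents do not settle that. A reader might also infer that the trial has a 5% chance of success. That figure applies only to a PEDT-only endpoint with equal case rates. It does not apply to topic raised, to PE identified by the GP, or to GP identification combined with the PEDT. Even under the PEDT-only reading, rates could differ between arms through treatment, or because unblinded GPs enrol patients after learning the reason for the visit.

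Nor can it be claimed that a consultation-based endpoint would have almost no missing data. GP forms are mailed in and 10% GP loss is expected.

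The defence does not remove the contradiction. One section gives its primary analysis two endpoints, and the definition that matches the model sentence is the 4-week PEDT. Nothing here is simply left to a fuller document: the article makes conflicting statements.

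**Conclusion.** The point holds in this form: the primary model as written targets a different endpoint from the one that the aim, the primary outcome and the sample size define, and the sections that could resolve it disagree on who identifies a case (GP or PEDT) and at which score (above 9, or 11). That follows from the text alone.

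The size is conditional. On a PEDT-only reading with equal case rates in the two arms, power falls to about 5% against the stated 90%, and the 20% patient loss affects the primary endpoint. If topic raised is modelled, 5% v 20% applies and the 600 planned patients give about 82% to 99% power over the stated ICC range, before losses. Because the ambiguity concerns what the trial's main result measures, it should be resolved before analysis.

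**What to change.** - In Statistical methods, make the dependent variable of the primary mixed model the outcome in the Outcome section: topic of PE raised at the index consultation, yes/no, as recorded on the GP questionnaire, in all included patients. The article does not list that questionnaire's items, so check that it records this.
- State whether discussions opened by the GP count. The outcome speaks of patients bringing up the topic, while the Intervention section trains GPs in systematic questioning. Either rule can be defended; the text should say which applies.
- Align Outcomes and measurements, Sample size estimation, Monitoring and the Discussion with that definition. In particular, say whether the interim analysis of the primary endpoint really needs the PEDT to be complete.
- Keep PEDT-defined PE as a secondary outcome with a single cut-off, reconciling above 9 with 11.

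The cost is wording only. The sample size does not change on this account, because it is already stated for topic raised.
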